### Sample size

There is no reference clinical data for the efficacy of DTM stimulation using a paddle-type lead placed on the rostral side of the SCI because there is only one case report [26]. Therefore, the sample size is not able to determine on statistical assumptions. Assume that there are 2 to 4 cases who meet the inclusion criteria of this study in a year. The sample size is set 10 as the number that can be achieved in 3 to 5 years.

### Concealment mechanism

The results of the allocation will be shown via the interactive web response system.

### Assignment of interventions: blinding

#### Who will be blinded?

Trial participants will be blinded to which group they are assigned.

#### Procedure for unblinding if needed

Not applicable. The study design is open label with only data analysts being blinded so unblinding will not occur.

### Plans to promote participant retention and complete follow-up

Medical interviews and adjustments of SCS will be booked for all patients.

### Confidentiality

The form used to code patients will be stored in a locked cabinet with logged access only available to the researchers and administrators responsible for the study.

### Plans for collection, laboratory evaluation, and storage of biological specimens for genetic or molecular analysis in this trial/future use

Not applicable.

### Statistical analysis

The primary outcome will be estimated as the probability of patients achieving more than 33% pain improvement on the VAS at 3 months after SCS system implantation. The secondary outcome analyses are as follows:A logistic regression analysis using stimulation timing (Stim-1, Stim-2), stimulation pattern (tonic, DTM), pre-VAS values for each stimulation, and interaction between stimulation timing and stimulation pattern as explanatory variables. The carryover effect is examined by testing the interaction term at a significance level of 10%. If a carryover effect is observed, an additional analysis will be performed using only Stim-1.Adjusted means and 95% confidence intervals (CIs) of the rate of change or amount of change for each item (VAS, SF-MPQ-2, PCS, QIDS-J, and SF-36^®^) are calculated for each evaluation time point including pre-implantation and post 1, 3, 6, 12, 18, and 24 months using linear mixed models with time points as fixed effects. The amount of change of each item at each time point is compared after using the Dunnet-Hsu correction for multiple comparisons.For the patients undergoing implantation, logistic regression will be performed to investigate the relationship between the efficacy of the SCS trial (DTM) and the effectiveness for 33% improvement on the VAS at 3 months after implantation.Preoperative factors associated with long-term effects are examined using logistic regression analysis as explanatory variables for the following items: sex, age (<60 years vs. ≥60 years), disease duration, pain site (arm, leg, lower back, back, chest), level of SCI (cervical, thoracic, lumbar), paralysis (none, mild, moderate, severe), sensory disturbance (hypoesthesia, allodynia, numbness), and Frankel classification (B, C, D, E).Probability of gait improvement is estimated, defining an improvement as 1 point or more in the FAC category. The probability of improved cases and the 95% CIs will be calculated at each evaluation time point.

Safety analysis will be performed by tabulating the number and probability of each event.

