### Study procedures

This trial consists of a two-step procedure. The first step is an SCS trial, and the second step is SCS system implantation. The lead locations for the SCS trial and SCS system implantation are the sides caudal and rostral to the SCI, respectively. In the SCS trial, two cylinder-type leads (Model 977A190; Medtronic Inc., Minneapolis, MN, USA) are to be inserted on the caudal side of the SCI under local anesthesia, so that the lead does not pass through the SCI. Once inserted, the two leads are directly sutured to the skin at the puncture sites without skin incision. The order of stimulation patterns of DTM or tonic is randomly assigned to two courses evenly (Fig. 1). One course is DTM stimulation (Stim-1), then tonic stimulation (Stim-2), and the other course is in reverse order. Each stimulation pattern is performed for two days. The stimulation off period is set as one day between Stim-1 and Stim-2 to washout previous stimulation effects (Stim-off).

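### The DTM-versus-tonic crossover analysis does not say how the pairing within patients is handled, and its five-parameter logistic model often cannot be fitted with 10 patients

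*Protocol article*

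**What the plan says.** Under Study procedures, every patient in the SCS trial receives both patterns: "One course is DTM stimulation (Stim-1), then tonic stimulation (Stim-2), and the other course is in reverse order". Allocation is balanced: "The order of stimulation patterns of DTM or tonic is randomly assigned to two courses evenly". Under Sample size, "The sample size is set 10 as the number that can be achieved in 3 to 5 years".

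Under Statistical analysis, the first secondary analysis is "A logistic regression analysis using stimulation timing (Stim-1, Stim-2), stimulation pattern (tonic, DTM), pre-VAS values for each stimulation", together with the "interaction between stimulation timing and stimulation pattern as explanatory variables". Then: "The carryover effect is examined by testing the interaction term at a significance level of 10" (per cent). "If a carryover effect is observed, an additional analysis will be performed using only Stim-1".

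The sentence does not name the binary outcome, and it mentions no patient effect, conditioning, clustered variance, or exact or penalised method. The next analysis in the same section does name linear mixed models. The missing-data section rules out any statistical compensation for missing values, so 20 outcomes is an upper limit.

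**The concern.** The order of stimulation is the only thing randomised in this trial. This is also the only listed analysis of the second clinical question in the Background, whether DTM relieves pain better than tonic stimulation. A two-period crossover earns its efficiency from the comparison within each patient. A logistic model with only the listed terms treats the two outcomes of a patient as independent. Its standard errors are then wrong, in opposite directions for the treatment effect and for the carryover test.

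A second problem is independent of the first. The model asks for an intercept and four coefficients from at most 20 yes/no outcomes. With so few events, some combination of covariates often predicts the outcome perfectly, and no finite odds ratio exists. The plan could then fail to deliver the estimate it promises.

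**Working it through.** **The plan's own figure.** The sample size rests on accrual: "Assume that there are 2 to 4 cases who meet the inclusion criteria of this study in a year". At 2 per year, 10 patients take 10/2 = 5 years; at 4 per year, 3 years yield 12. The figure of 10 is consistent with this, and no power calculation is claimed.

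**Inputs.** Patients: 10, about 5 per order. Outcomes: 10 × 2 = 20 at most. Parameters: intercept, timing, pattern, pre-VAS and interaction = 5. Tonic success rate: about 30% (Background). Assumed, because the documents do not give them: the outcome (taken as the responder definition under Primary outcome), the DTM response rate and the within-patient correlation ρ.

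**Events.** At a 30% response rate, 20 × 0.30 = 6 events, and 6/5 = 1.2 events per parameter.

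**(a) Standard errors if pairing is ignored.** In a 2×2 crossover the timing-by-pattern interaction is the contrast between the two orders, so it is a between-patient quantity. With outcome variance σ² and n patients, on a linear scale:

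- DTM minus tonic: true variance 2σ²(1−ρ)/n, assumed 2σ²/n. Model SE / true SE = 1/√(1−ρ).
- Order contrast: variance of a patient's mean is σ²(1+ρ)/2, assumed σ²/2. Model SE / true SE = 1/√(1+ρ).

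The logistic model itself was simulated at 200 patients, where fitting is not a problem, with 30% response on both patterns. Patient logit SDs of 1, 2 and 3 correspond to ρ of 0.16, 0.38 and 0.52 between the binary outcomes.

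| Patient logit SD | 1/√(1−ρ) | Simulated SE ratio, DTM v tonic | 5% test rejects | 1/√(1+ρ) | Simulated SE ratio, carryover | 10% test rejects |
|---|---|---|---|---|---|---|
| 1 | 1/√0.84 = 1.09 | 1.07 | 3.1% | 1/√1.16 = 0.93 | 0.91 | 14% |
| 2 | 1/√0.62 = 1.27 | 1.25 | 1.5% | 1/√1.38 = 0.85 | 0.81 | 18% |
| 3 | 1/√0.48 = 1.44 | 1.41 | 0.6% | 1/√1.52 = 0.81 | 0.77 | 19% |

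The formula and the simulation agree in direction and closely in size. With no within-patient correlation both tests are correct (5.5% and 10.1%). At 10 patients, in runs that could be fitted, the carryover test rejected 3 to 12%, so small-sample behaviour partly hides the inflation.

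**(b) Whether the model can be fitted.** Simulation of 10 patients with the five listed parameters, checking each data set for complete or quasi-complete separation:

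| Tonic / DTM response | No finite fit |
|---|---|
| 30% / 30% | 45–53% |
| 30% / 50% | 37–39% |
| 30% / 70% | 52–53% |
| 20% / 40% | 58–64% |
| 50% / 50% | 21–24% |

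The Stim-1-only analysis (3 parameters, 10 outcomes) had no finite fit in 16 to 43%. In a separate simulation built from VAS reductions (5+5 patients, baseline about 65, SD of reduction 20), the full model failed in about 30 to 56% of trials and in 2 to 9% once the interaction was removed. The interaction is therefore the main cause.

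**What a paired VAS analysis offers.** For an assumed 0.8 SD difference and 10 patients, power was:

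| ρ | Paired | Same linear model without patient |
|---|---|---|
| 0 | 35% | 38% |
| 0.3 | 48% | 39% |
| 0.5 | 62% | 38% |
| 0.7 | 81% | 35% |

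The paired analysis could be fitted in every run and held its 5% and 10% error rates.

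**The case against.** The best defence is that the sentence lists explanatory variables. A random intercept, a clustering unit or a conditioning stratum is not one, and a journal article may leave it to the full protocol. That stands in part. A reader might infer that the pairing is certainly discarded; the article supports only that no handling of it is named. It carries some weight that a mixed model is named for the next analysis and not for this one. The fitting problem does not depend on this, because a patient term does not remove separation.

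Other stronger readings also go too far:

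- A reader might expect false claims for DTM. The treatment error is conservative; only the carryover test rejects too often.
- The linear formula at ρ of 0.3, 0.6 and 0.8 gives 1.20, 1.58 and 2.24. The planned model is logistic, for which the simulated range is 1.07 to 1.41, and the documents give no ρ.
- A reader might set the very low power of the planned DTM coefficient beside the high power of a paired VAS test. That changes three things at once: binary to continuous, interaction removed, pairing added. With 0/1 coding and an interaction, that coefficient is also the effect in one period only, and the article fixes neither the coding nor the test. The gain from pairing alone is modest at ρ = 0.3 and large only at higher ρ.

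Finally, the Discussion justifies the 33% threshold as clinically meaningful, so responder results should be kept. The trial is exploratory and its sample size was not set by power, which limits how serious this is.

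**Conclusion.** The point holds as two distinct defects in one secondary analysis. If pairing is ignored and ρ is positive, the DTM-versus-tonic standard error is about 1.07 to 1.41 times too large, and the 10% carryover test rejects about 14 to 19% in large samples, partly masked at 10 patients. Separately, the five-parameter model has no finite fit in roughly 20 to 65% of plausible trials, and the Stim-1-only analysis in about 16 to 43%. These ranges rest on the assumed outcome definition, response rates and patient-level variation. The fitting problem remains even with no within-patient correlation.

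It should be fixed before analysis, but it does not threaten the trial: the primary outcome is a single proportion that this model does not touch.

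**What to change.** Make the main DTM-versus-tonic analysis a period-adjusted paired analysis, or a linear mixed model, of the VAS (or VAS change) in each stimulation period. Use pattern and period as fixed effects, patient as a random effect and small-sample degrees of freedom, and report the mean difference with its 95% CI. Under an assumed 15 to 20 point DTM advantage, this raised power from about 22–58% (unpaired linear model) to 44–99%.

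Keep the clinical threshold by reporting responders (more than 33% reduction) per pattern as a descriptive paired table. Do not rely on a McNemar test: the exact version needs at least 6 discordant patients, all in one direction, for p<0.05 (2 × 0.5⁶ = 0.031; with 5, 2 × 0.5⁵ = 0.0625).

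If carryover is still examined, test it as a between-patient contrast of the two orders with the matching error term, and leave the interaction out of the model that estimates the treatment effect.

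The cost is one rewritten paragraph. The VAS is already recorded during the SCS trial, so no new data, visits or patients are needed. The downside is that the main crossover summary becomes a mean VAS difference and not a responder odds ratio.

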### Secondary outcomes

The secondary outcomes are as follows: (1) evaluation of effectiveness of DTM and tonic stimulations in the SCS trial; (2) evaluation of changes of assessment scores, VAS, SF-MPQ-2, PCS, QIDS-J, and SF-36^®^, at 1, 3, 6, 12, 18, and 24 months from SCS system implantation; (3) relationship between the result of the SCS trial and the effect 3 months after SCS system implantation; (4) evaluation of preoperative factors associated with a long-term effect, defined as continuing for more than 12 months; (5) evaluation whether there is improvement of motor function using the gait function scale (FAC) at 1, 3, 6, 12, 18, and 24 months from SCS system implantation; and (6) adverse events related to this study 3 months after SCS system implantation.

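### The only DTM-versus-tonic model contains the timing-by-pattern interaction with no stated step to remove it, so the effect depends on coding and is often non-estimable with about five patients per cell

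*Protocol article*

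**What the plan says.** The first item under Secondary outcomes in the protocol article is "evaluation of effectiveness of DTM and tonic stimulations in the SCS trial". The analysis for it, under Statistical analysis, is "A logistic regression analysis using stimulation timing (Stim-1, Stim-2), stimulation pattern (tonic, DTM"), together with "pre-VAS values for each stimulation, and interaction between stimulation timing and stimulation pattern as explanatory variables". This is the only model given for the comparison.

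The interaction serves as the carryover test, at the 10% level. One consequence of that test is written down: "If a carryover effect is observed, an additional analysis will be performed using only Stim-1". The section does not say that the interaction is taken out when the test is negative, that the pattern effect is averaged over the two periods, or how the factors are coded.

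Study procedures states that "The order of stimulation patterns of DTM or tonic is randomly assigned to two courses evenly". Under Sample size, the target is 10 patients, set by feasibility.

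**The concern.** Once pattern and its interaction with timing are both in a model, there is no single pattern effect until a contrast is defined. The model allows one DTM-versus-tonic effect in Stim-1 and another in Stim-2. What is reported as the pattern effect then depends on coding or on a contrast that the article does not give.

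The second issue does not depend on coding. Two timings, two patterns and their interaction give each of the four cells its own free parameter. With about five patients per cell, a cell in which everyone or no one responds is not rare, and its log odds is then infinite under maximum likelihood.

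At stake is the trial's only randomised comparison. It could be reported from one period, with an odds ratio that changes with a software default, or it could have no finite estimate.

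**Working it through.** **Inputs.** From the article: 10 patients, even allocation to two orders, two periods each, logistic regression with the terms above and no patient term named. Assumed: 5 patients per order, all completing both periods; a binary response; response probabilities of 0.3 to 0.7; the 20 patient-periods treated as independent. The article gives no power or effect size for this comparison, so there is no figure to reproduce.

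**1. What the coefficient means under 0/1 coding.** The log odds is a + b·timing + c·pattern + d·timing·pattern. In the reference period timing = 0, so c is the DTM effect in that period alone. If Stim-2 is the reference level, c is the Stim-2 effect. Either way, about 5 patients are set against 5 others.

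**2. Precision at response 0.5.** The variance of a cell's log odds is 1/(5 × 0.25) = 0.8.
- One-period contrast: SE = √(0.8 + 0.8) = 1.26.
- Average of the two period contrasts: SE = √(4 × 0.8)/2 = 0.89.
- Ratio: 1.41.
- 95% limits: a factor of exp(1.96 × 1.265) = 11.9 either way, against exp(1.96 × 0.894) = 5.8.

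**3. Example fit without pre-VAS.** Take Stim-1 with DTM 3/5 and tonic 2/5, and Stim-2 with DTM 4/5 and tonic 1/5. The interaction is not significant (p = 0.34).

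| Analysis | Log odds ratio | SE |
|---|---|---|
| Interaction kept, 0/1 coding, Stim-1 reference | 0.811 | 1.291 |
| Stim-1 data only | 0.811 | 1.291 |
| Interaction kept, ±0.5 coding | 1.792 | 1.021 |
| Interaction removed | 1.695 | 0.976 |

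With Stim-2 as reference, the same data give ln[(4/1)/(1/4)] = 2.773. The odds ratio read from the 0/1-coded fit is therefore 2.25 or 16, depending on the reference level.

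**4. With pre-VAS.** The pre-VAS slope draws on both periods, so the identity with the Stim-1-only fit becomes approximate. In simulations of 400 patients (400 replicates, assumed patient SD of 0 to 3 on the logit scale, assumed log odds ratio of 1.0), the 0/1-coded estimate correlated 0.997 to 0.999 with the Stim-1-only estimate.

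**5. Non-estimability with the interaction, any coding.** The probability that a cell of five is 0/5 or 5/5 is e(q) = q⁵ + (1−q)⁵.
- e(0.5) = 0.0625 and e(0.3) = e(0.7) = 0.1705.
- The period-averaged contrast uses all four cells, so one extreme cell is enough. The probability is 1 − (1 − e)⁴.
- All rates 0.5: 1 − 0.9375⁴ = 23%.
- Rates of 0.3, or 0.3 against 0.7: 1 − 0.8295⁴ = 53%.

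Adding pre-VAS does not rescue an extreme cell, because that cell still has its own free parameter.

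**6. Non-estimability without the interaction.** A single extreme cell no longer matters. The pattern effect is lost mainly when all ten observations on one pattern agree, or when the two cells of one order are opposite extremes. Summing over all 3⁴ = 81 combinations of none, all or mixed in the four cells gives about 1% (both rates 0.5) to about 10% (0.3 against 0.7).

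**7. Effect of the independence assumption.** Positive within-patient correlation makes the two cells of one order extreme together and so lowers the figure in step 5. In the limiting case where every patient responds identically in both periods, it is 1 − (1 − e)²: 12% at 0.5 and 31% at 0.3.

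**The case against.** The strongest reply is that the one-period result depends on a coding the article does not state. Sum-to-zero coding, or a period-averaged contrast from the same model, recovers almost all the precision: SE 1.021 against 0.976 in the example, and 0.913 against 0.913 when the two periods show the same effect. A condensed article may leave coding and contrasts to the full plan. The wording also treats the Stim-1-only analysis as something additional, which suggests that the main analysis is meant to use both periods. All of this stands. A reader might infer that the plan reports a one-period comparison on half the data; the article does not support that.

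The reply does not reach the saturation problem, which arises under every coding. Nor is this only a matter of detail left elsewhere. The article itself lists the model terms, the test level and the follow-up rule, and that rule covers only the case where carryover is found.

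Two further inferences are tempting and should not be drawn. One is that the loss can be sized from a paired analysis on the VAS scale; the plan's model is logistic and names no patient term. The other is that adding a patient term would leave the problem untouched. That holds for a random patient effect. In this design timing × pattern equals (order − 1 + timing + pattern)/2, with order coded 1 for tonic first, and fixed patient effects absorb order. The interaction then cannot be estimated and has to be dropped.

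**Conclusion.** The concern holds in a limited form. As written, the model for the DTM-versus-tonic comparison retains the interaction, and the reported effect is not fixed.

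If 0/1 coding is used, the standard error of the log odds ratio is about 41% larger (1.26 against 0.89 at response 0.5), and the estimate describes whichever period is the reference. Other codings avoid this, so the loss is possible but not inevitable.

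Under any coding, the risk of a non-estimable averaged effect is about 23–53% with the interaction and about 1–10% without it. These figures assume five patients per order, response rates of 0.3 to 0.7, no pre-VAS and independent observations. Within-patient correlation would lower the first range, as step 7 shows.

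The impact is modest. The comparison is a secondary outcome in an exploratory trial of 10 patients, the article says that "the sample size is not able to determine on statistical assumptions", and even the better estimate has 95% limits of nearly sixfold either way. The primary outcome is not affected.

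**What to change.** State in the Statistical analysis section that the DTM-versus-tonic effect is estimated from the model with pattern, timing and pre-VAS, without the interaction, using both Stim-1 and Stim-2. Fit the timing-by-pattern interaction only in a separate model, reported descriptively as a look at carryover, and do not read the pattern effect from that model.

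The cost is one or two sentences, with no new data, visits or patients. The change lowers the risk of a non-estimable effect but does not remove it.

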## Methods/design

### Study design

This is a prospective, single-center, open-label, randomized, two-way crossover, exploratory trial.

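### The 10% carryover test that triggers a Stim-1-only analysis is an unreliable gate at about 5 patients per sequence, and the plan does not say which result then governs

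*Protocol article*

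**What the plan says.** The Study design section describes the trial as follows: "This is a prospective, single-center, open-label, randomized, two-way crossover, exploratory trial". Under Study procedures, "The order of stimulation patterns of DTM or tonic is randomly assigned to two courses evenly", and "Each stimulation pattern is performed for two days", with one stimulation-off day between the periods as washout. Under Sample size, "The sample size is set 10 as the number that can be achieved in 3 to 5 years". The same section explains that the number has no statistical basis: "Therefore, the sample size is not able to determine on statistical assumptions".

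The effectiveness of DTM and tonic stimulation in the SCS trial is secondary outcome (1). The Statistical analysis section assigns it a logistic regression on stimulation timing, stimulation pattern, the pre-VAS value for each stimulation, and the timing-by-pattern interaction. Two sentences then set the carryover rule: "The carryover effect is examined by testing the interaction term at a significance level of 10" per cent, and "If a carryover effect is observed, an additional analysis will be performed using only Stim-1".

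The section gives no significance level for the DTM-versus-tonic test itself, and does not say how to conclude if the crossover and Stim-1 analyses disagree.

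**The concern.** A significance test for carryover that leads, when positive, to a first-period analysis has the structure of the two-stage crossover procedure. It has two known weaknesses. The carryover test is a between-patient comparison, so in a small trial it can neither establish nor exclude carryover. It also shares its data with the first-period contrast, so a chance imbalance between the sequence groups both fires the gate and pushes the Stim-1 comparison away from zero. The Stim-1 result is therefore least trustworthy in exactly the trials where the plan calls for it.

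At stake is the trial's only randomised comparison, which addresses the second clinical question in the Background section (DTM against conventional tonic stimulation). If a triggered Stim-1 result were allowed to carry that conclusion, the answer would depend partly on a chance gate.

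**Working it through.** **The plan's own figure.** There is no power or error calculation to reproduce. The 10 patients come from feasibility: 10/4 = 2.5 years to 10/2 = 5 years at 2 to 4 patients a year, which broadly fits the stated 3 to 5 years.

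**Inputs from the protocol article.** Two periods and two patterns; 10 patients allocated evenly, so about n = 5 per sequence; carryover test at 10%.

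**Assumptions not in the document.** Continuous VAS with SD s; two-sided 5% treatment test; within-patient correlation ρ of 0.3 to 0.8.

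**1. What the interaction measures.** Let sequence A receive DTM then tonic, and sequence B tonic then DTM. The interaction is (DTM₁ − tonic₁) − (DTM₂ − tonic₂) = (DTM₁ + tonic₂) − (tonic₁ + DTM₂). This is the difference between the sequences in patients' two-period sums, a comparison of 5 with 5.

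**2. Power of the carryover test.** A patient's sum has variance 2(1+ρ)s², so the standard error of the contrast is s√[4(1+ρ)/5]. For a 1 SD carryover the non-centrality is 1/√[4(1+ρ)/5], for example 1/√1.2 = 0.91 at ρ = 0.5. The non-central t with 8 df gives the power in the table. For a 0.5 SD carryover, simulated power is only 12% to 13%.

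**3. Link with the Stim-1 contrast.** The correlation between a patient's Stim-1 value and two-period sum is (1+ρ)/√[2(1+ρ)] = √[(1+ρ)/2].

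**4. Error rates.** Simulated 2×2 crossovers with no treatment effect and no carryover: t-test on sums at 10%, t-test on period differences at 5%, Stim-1 t-test at 5%.

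| ρ | 0.3 | 0.5 | 0.7 | 0.8 |
|---|---|---|---|---|
| Power, 1 SD carryover | 23% | 22% | 20% | 20% |
| Correlation, gate with Stim-1 contrast | 0.81 | 0.87 | 0.92 | 0.95 |
| False positive, Stim-1 test, given gate fired | 29% | 34% | 41% | 44% |
| Overall error, Stim-1 replaces crossover result | 7.4% | 7.9% | 8.7% | 8.8% |
| Overall error, either result may count | 7.6% | 8.1% | 8.9% | 9.0% |
| Overall error, crossover result always governs | 5.0% | 5.0% | 5.0% | 5.0% |

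Separate runs of the conditional rate differ by up to about one percentage point.

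**5. With baseline adjustment.** Adding pre-stimulation VAS to all three tests (four equally correlated readings) lowers the conditional false-positive rate to about 23% and the overall error under replacement to 6.7% to 6.8%. The gate also gains power. The residual variance of the sum given the summed baselines is [2(1+ρ) − 8ρ²/(1+ρ)]s², which is 2.6 − 0.55 = 2.05s² at ρ = 0.3 and 3.6 − 2.84 = 0.76s² at ρ = 0.8. The non-centralities for 1 SD are 1/√(2×2.05/5) = 1.10 and 1/√(2×0.76/5) = 1.81. By simulation, power is about 24% and 46%. This holds for a carryover that leaves the pre-Stim-2 VAS unchanged.

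**6. Precision.** The Stim-1 contrast has variance 2s²/5, and the within-patient estimate (1−ρ)s²/5. The ratio is 2/(1−ρ), which is 4 at ρ = 0.5 and 6.7 at ρ = 0.7 unadjusted. With baseline adjustment it is 3.0 to 3.5 over the same range.

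**7. Logistic form.** A binary-outcome simulation used the stated terms without pre-VAS or a patient term, with response rates of 30% or 50% and ρ from 0 to 0.9. The interaction test rejected 16% to 33% of the time with no carryover, instead of 10%. Overall error was 8% to 12% when the Stim-1 result could replace or supplement the crossover result.

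**The case against.** The strongest reply is textual. A reader might infer that the plan switches to Stim-1 and discards the within-patient comparison. The Statistical analysis section does not say so: it calls the Stim-1 analysis additional, and nothing withdraws the crossover regression. If that regression governs, overall error is not inflated. This stands. What remains is that the article states a trigger without saying which result governs, and that the false-positive rate of a triggered Stim-1 test applies to that analysis whatever its status.

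A second reply is that unadjusted t-tests are not the planned model. This also stands. Adjustment for pre-VAS shrinks the inflation to under 2 percentage points even under replacement and lets the gate detect more. The conditional rate of about 23% is still more than four times nominal, and the gate still misses a 1 SD carryover more often than not.

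A reader might also take the pre-VAS adjustment as a fault because it could absorb a carryover that shifts the Stim-2 starting level. The document does not support that: such adjustment may equally protect the treatment estimate. Nor does the absence of a named patient term show that pairing is ignored, since the article may simply condense the model.

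Finally, the trial is exploratory, the comparison is secondary with no stated significance level, and the design has a washout day. All of this limits the consequence.

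**Conclusion.** The concern holds as a moderate one. The 10% interaction test is a poor basis for deciding whether to run or rely on a Stim-1 analysis. Unadjusted, it finds a 1 SD carryover about 20% to 23% of the time, and once it fires with nothing there, the Stim-1 test is falsely positive about 29% to 44% of the time (about 23% baseline-adjusted). The overall consequence depends on a rule the article leaves open: about 7% to 9% error if the Stim-1 result may replace or add to the conclusion, and 5% if the crossover result always governs.

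The figures rest on about 5 patients per sequence, a continuous VAS, an assumed 5% treatment test and assumed correlations of 0.3 to 0.8. They show direction and rough size, not the operating characteristics of the planned logistic model. The primary outcome, the responder rate at 3 months after implantation, is untouched.

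**What to change.** In the Statistical analysis section:

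- Remove the 10% test as a trigger.
- State that the period-adjusted, within-patient, two-period DTM-versus-tonic estimate governs whatever the interaction shows.
- Report the interaction estimate with its confidence interval, and pre-Stim-1 and pre-Stim-2 VAS by sequence, as descriptive checks on washout.
- Show Stim-1 results descriptively in all cases, not only after a positive test.

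This changes wording only; no data collection or design feature is affected. With the gate gone, the unadjusted model gives 5.0% error and 65%, 79% and 95% power for a 1 SD treatment effect at correlations 0.3, 0.5 and 0.7, against 29% for Stim-1 alone.

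The cost is that a real carryover biases the two-period estimate by half its size. In the unadjusted simulation, a 1 SD carryover with no treatment effect makes the crossover test falsely positive 22%, 29% and 44% of the time at those correlations. The gate is weak protection: it misses such a carryover about four times in five unadjusted, and even full replacement by Stim-1 lowers those rates only to 19%, 26% and 38%. Replacement would help more if baseline adjustment raised the gate's power, but the plan does not specify replacement.
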